In the present study, we will address this issue by systematically investigating the effects of a-tDCS over the premotor and primary motor cortices and the synergetic effects of a-tDCS over the premotor and primary motor cortices and c-tDCS over the cerebellum. As it is thought that tDCS is most effective when combined with a behavioural task [36], tDCS will be administered during simultaneous treadmill walking, because a recent study reported more pronounced effects after this task compared to other physical tasks in PD [37]. This ensures that the neural circuits, and particularly M1, are active during application of the tDCS. In this study, we also took advantage of the same anode electrode parameters used in studies by Kaski et al. [30, 33, 35, 38]. Applying bilateral a-tDCS over the premotor and primary motor cortices and comparing the effects of both active (small) and functionally inert (large) cathodes over the cerebellum in PD could disentangle the location of possible tDCS effects on gait abilities in PD. We hypothesize that a large cathode will render stimulation over the cerebellum inactive (i.e. a monopolar M1 set-up), whereas a smaller cathode will exert additional inhibitory effects on the cerebellum (i.e. a bipolar M1 cerebellar set-up) [39]. To our knowledge, no study to date has analysed the gait parameters and electromyography (EMG) of the lower limb focusing specifically on different bilateral tDCS montages.

Thus, this randomized placebo (“sham tDCS)” controlled study aims to examine the short-term effects of (1) monopolar bilateral a-tDCS over the premotor and primary motor cortices (exploratory aim 1); (2) bipolar bilateral a-tDCS over the premotor and primary motor cortices and cerebellum cortex (exploratory aim 2) while walking on a treadmill on gait speed as the main outcome measure and other gait kinematics and EMG in people with PD when optimally medicated. The findings will be reported and disseminated through peer-reviewed journal publication and conference presentations. The results of the study will also be presented for PD support groups who contributed in participant recruitment.

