### Statistical analysis

Sample characteristics will be summarized into the number of non-missing data, mean, standard deviation, minimum, maximum and 95% confidence interval, for quantitative variables. Number of non-missing data, frequency and proportion will be used for the description of categorical variables.

Gait speed will be the primary outcome in this study. The possible effects of participants’ physical activity level at baseline on gait speed will be investigated by performing an analysis of the Pearson correlation between gait speed (estimated using the Vicon system before applying tDCS) and physical activity level.

We will examine the within-visit effects of each tDCS on gait speed as the primary outcome and the gait kinematics and TUG time as secondary outcomes using a paired *t* test to compare pre- and post-tDSC measures.

The main effect of the three tDCS conditions (monopolar bilateral tDCS, bipolar bilateral tDCS and sham tDCS) on gait speed and gait kinematics will be examined through a linear mixed model (LMM) with random intercepts. The LMM model will contain participants nested in sequence as a random effect. In order to investigate the carry-over effect, we will compare three measures before the three tDCS procedures using one-way analysis of variance (ANOVA). When appropriate, post hoc comparisons will be carried out using a Tukey correction for multiple comparisons. The LMM will also be conducted to examine the potential interaction of time (levels: pre- and post-tDCS) and tDCS (levels: monopolar bilateral tDCS, bipolar bilateral tDCS and sham tDCS) in the two conditions of even and uneven surfaces. *P* values less than 0.05 will be considered significant, and for valid interpretation of the results the confidence interval will be reported as an indication of effect size [63]. All analysis will be performed using SPSS software (version 23; IBM Corporation, Armonk, NY, USA). Missing data will be handled using a simple imputation method [58]. This Statistical Analysis Plan (SAP) will be provided before opening the database.

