## Discussion

During the last few years, the treatment of PD has shifted from a focus on pharmacological intervention towards investigation of different non-pharmacological approaches such as tDCS. Such approaches have been motivated due to the side effects of PD medications which have included dyskinesia [28, 64, 65] and freezing of gait [2]. tDCS has been suggested as an alternative and promising adjunct treatment for PD. However, results of previous clinical trials in improving gait in PD have been equivocal, and an optimum tDCS montage has not been established. Therefore, we will systematically investigate the effects of two different montages administered during treadmill walking and their effects on gait and EMG parameters. To do so, we will use a modified montage used by Kaski [30, 33, 35, 38] to determine whether the synergetic effects of a-tDCS over both the premotor and primary motor cortices and c-tDCS over the cerebellum are more beneficial compared to the effects of a-tDCS over the premotor and primary motor cortices in PD. Furthermore, the comparison of the effects of the two montages on behavioural changes will provide information for further establishing the exact role of a-tDCS with a large electrode (monopolar set up) and a-tDCS with small cathode electrode (bipolar set-up) on gait in PD. Indeed, our initial evaluation of EFI modelling (Fig. 3) shows that the small cathode electrode over the cerebellum results in more pronounced current flow to the cerebellum, affecting its posterior, inferior and lateral aspects and the vermis of the cerebellum, while the EFI over the cerebellum with the large cathode electrode is on the lateral edges of the cerebellum.

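### Gait speed is tested several ways at 5% with no deciding test named; if the main effect or the interaction may count as success, the false-positive rate runs from 5% to about 24%, depending on an unstated model

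*Protocol article*

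**What the plan says.** In the protocol article, Statistical analysis, "Gait speed will be the primary outcome in this study". Three kinds of test are then applied to it.

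- Paired t tests, pre against post, within each condition: "We will examine the within-visit effects of each tDCS on gait speed as the primary outcome".
- A condition main effect. "The main effect of the three tDCS conditions (monopolar bilateral tDCS, bipolar bilateral tDCS and sham tDCS) on gait speed and gait kinematics" is to be examined in a linear mixed model with random intercepts, with participants nested in sequence as the random effect. The section does not say whether the response is the post value, pre and post pooled, or the change.
- An interaction: "The LMM will also be conducted to examine the potential interaction of time (levels: pre- and post-tDCS) and tDCS", to be looked at "in the two conditions of even and uneven surfaces".

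One threshold, P below 0.05, applies throughout. Tukey is planned for post hoc comparisons when appropriate.

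The Background sets two unranked aims, one per montage, in a sham-controlled study; the second is "bipolar bilateral a-tDCS over the premotor and primary motor cortices and cerebellum cortex (exploratory aim 2"). The Discussion adds a montage-against-montage question: whether the combined motor and cerebellar effects "are more beneficial compared to the effects of a-tDCS over the premotor and primary motor cortices in PD". The Sample size section takes its effect size from active against sham stimulation and names no montage.

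**The concern.** The three kinds of test answer different questions. A paired t test has no sham comparison, so a practice or treadmill effect common to all sessions can make it significant. A main effect on pooled pre and post values compares averages, half of which were measured before any current was applied. A difference already present before stimulation can produce it, and only half of a true post-stimulation effect enters it. The interaction compares the pre-to-post changes, which is the short-term effect that the aims describe.

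With one threshold and no order among the tests, a significant result on any of them could be presented as the primary finding. The error rate then depends on which response variable and error term the main-effect model uses, and the text does not fix either.

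**Working it through.** **The plan's own figure.** The only error rate stated is 0.05 per test; no overall rate is given. The sample size is 18. The Sample size section allows 20% drop-out, so about 15 completers (15 × 1.2 = 18) is used as the lower case.

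**Simple bound.** Two independent tests at 5%: 1 − 0.95² = 0.0975. The sum bound is 0.10.

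**Why the main effect and the interaction differ.** Let a montage add δ at post, with residual SD σ and visit-to-visit SD v. Per participant, against sham:

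- Pooled main effect: expected difference δ/2, variance 2(v² + σ²/2) = 2v² + σ².
- Interaction (difference in change): expected difference δ, variance 4σ².

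With v = 0 both have signal-to-noise δ/(2σ), so they have equal power. They use independent parts of the data, so they often disagree.

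**Why visit variance matters.** The random-intercept model has no visit term. In balanced data its 5(n − 1) residual df pool 2(n − 1) df with mean square σ² + 2v² and 3(n − 1) df with mean square σ², giving σ² + 0.8v². The main effect needs σ² + 2v² as its error and the interaction needs σ². With σ = 0.045 and v = 0.08:

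- Main-effect F is inflated by (0.002025 + 0.0128)/(0.002025 + 0.00512) = 2.07.
- Interaction F is deflated by 0.002025/0.007145 = 0.28.

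At v = 0.03 the factors are 0.003825/0.002745 = 1.39 and 0.002025/0.002745 = 0.74.

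**Simulation under no effect.** 40,000 trials per setting, three conditions, pre and post measures, one surface, n = 15 and 18. Assumed SDs in m/s (the article gives none): participant 0.20, residual 0.045, visit 0 to 0.08.

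| How the main effect is run, with the interaction as second route | Either significant |
|---|---|
| Change scores (same test as the change-score interaction) | 5% |
| Post values only, no visit variance | 8.3% to 8.5% |
| Pre and post pooled, no visit variance | 9.5% to 9.7% |
| Post values only, visit SD 0.03 to 0.08, interaction without a visit term | 5.1% to 6.4% |
| Post values only, visit SD 0.03 to 0.08, interaction on change scores | 8.9% to 9.6% |
| Pooled, visit SD 0.03 to 0.08, no visit term | 13% to 24% |

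In the last row the main effect alone rejects in 11% to 24%. That excess comes from the wrong error term, not from having two tests.

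**Further routes.** The pooled main effect plus an interaction on each surface, with no visit variance, gives 12.5% to 14.1% (three independent tests: 1 − 0.95³ = 14.3%). On one surface, adding the paired t tests of the two active conditions to the pooled main effect and interaction gives 16% to 31%. If all three conditions, sham included, gain 0.05 m/s, at least one test in that last set is significant in 98.9% of trials although tDCS does nothing.

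**Disagreement when an effect exists.** With a true gain of 0.05 m/s in one or both active conditions and n = 15, the pooled main effect and the interaction reach different verdicts in 44% to 48% of trials; post-only and change-score tests differ in 32% to 36%.

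**The case against.** **Doubling.** A reader might infer that the false-positive rate simply doubles. The documents do not support that. They never say that a significant result on either test makes the trial positive, and they do not state the response variable. Doubling is one cell of a range that starts at no inflation. If success also requires a Tukey-significant contrast against sham after a significant omnibus test, the either-test rate at n = 18 without visit variance is 6.3%, or 5.7% with a post-only main effect.

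**Contrasts.** A reader might also infer that no montage contrast is planned, or that an omnibus result driven only by one montage differing from the other would be called positive. Tukey over three conditions covers all three pairs, including each montage against sham, and no sentence makes an omnibus P value sufficient. What is missing is which model those contrasts belong to and which of them decides.

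**Disagreement.** These rates mostly reflect moderate power. Two near-independent tests with 57% power each disagree in 2 × 0.57 × 0.43 = 49% of trials. They show that the choice matters at such effects, and nothing more specific to this trial.

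**Order and timing.** The condition effect comes first, and the interaction is introduced as an addition. That suggests an order but states none, and the paired t test is the analysis tied most directly to the primary outcome. The section promises the analysis plan before the database is opened, so it cannot be said that the choice will be made after seeing the data. But the section calls its own text that plan, and the text gives the tests equal standing.

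**Exploratory aims.** Both aims carry that label, which softens the consequence. It does not remove it: the article also declares a primary outcome, a calculation at 80% power and a 5% significance rule.

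**Conclusion.** The point stands in this form: the plan gives gait speed several non-equivalent tests at 5% and does not say which decides, and Tukey does not reach across them. If pre and post values are pooled, the main effect is the wrong test for the question. If the main effect or the interaction may count as success, the error rate on one surface runs from 5% to about 24%.

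That range rests on the assumed SDs, balanced complete data, two-sided tests, and success on either test being allowed. Its upper end (13% to 24%) also needs pooled values and visit-to-visit variance that the model omits. The weakness should be corrected, because the error rate turns on choices that the text leaves open. It does not show that the trial will reach a false conclusion.

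**What to change.** In Statistical analysis, name one primary analysis: the between-condition difference in pre-to-post change in gait speed on one named surface. Analyse it as change scores, or in the pre/post mixed model with a visit-within-participant random intercept, so that the error term is valid. In simulation the single change-score test keeps its 5% level (4.8% to 5.1%).

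Decide it by the Tukey-adjusted contrasts the plan already provides: monopolar minus sham, bipolar minus sham, and bipolar minus monopolar. State that a montage is called effective only if its contrast with sham is significant. Label the condition main effect, the other surface and the within-condition paired t tests as secondary or descriptive.

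This costs a few sentences before the database is opened, with no new data or participants. The small downside is losing the extra chances of a positive primary result.

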### Primary and secondary outcomes

The primary outcome will be gait speed, and secondary outcomes include other gait kinematics, muscle activation and functional mobility (Table 1).

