#### Pre- and post-tDCS assessments

##### Three-dimensional gait assessment

Objective gait evaluation will be performed using a typical 3D assessment relying on motion capture [53, 54]. Gait speed as the primary outcome and all kinematic data will be collected using the Vicon system (Nexus 2.6; Vicon, Oxford, UK) including 12 cameras recording markers at 200 Hz within a calibration volume (e.g. L:9.3 × W:2.6 × H:2.5 m).

A total of 39 spherical markers (14 mm) will be positioned over body landmarks, based on a modified Helen Hayes marker set [3], including the head (forehead and back of the head); trunk (C7 spinus process, tenth thoracic vertebra, right scapula, jugular joint and xiphoid process); hips (anterior superior Iliac spine and posterior superior iliac spine); upper limbs (lateral border of acromion, upper arm, olecranon process of the humerus, lower arm, radial and ulnar styloids and second metacarpal head); and lower limbs (thigh, tibia, knee, ankle, second metatarsal head). Markers will be attached directly onto the skin using double-sided and hypafix tape. Marker placement will be performed by the same researcher in each session to minimize inter-tester variability. The 3D position of the markers will be expressed in the Global Coordinate System (GCS) placed approximately 1.3 m on the right side and 4.6 m behind the centre of the 10-m straight walkway.

First, the participant will be asked to walk naturally 10 times over the walkway to establish his/her self-selected walking speed. This speed will be used to set the treadmill speed during the tDCS sessions. Next, the participant’s anthropometrics will be measured and entered into the Vicon Nexus software, including body mass, height, leg length, knee and ankle width, elbow and wrist width and hand thickness.

Then, an initial recording of the participant standing still in the middle of the capture volume will be conducted for static calibration to facilitate automated detection and tracking of markers. Finally, the participant will be asked to walk six times in a straight line, over even and uneven surfaces on the walkway located in the middle of the calibration volume. Sufficient rest will be allowed in between trials to avoid participant’s fatigue.

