### Sample size

In preparation for the development of the protocol, the required sample sizes were calculated using Power Analysis and G* Power version 3.0. based on the primary outcome of gait velocity (measured by a 10-m timed walk, Kaski et al. [30]) and considering previously published cut-points for clinically meaningful difference in gait speed in people with PD: 0.02, 0.06 and 0.1 for small, moderate and large changes respectively [60]. The effect size derived from their study reflects the difference between a-tDCS and sham tDCS combined with physical training on gait velocity. To detect the difference followed by Kaski and considering a significance level of 5%, statistical power at 80%, significance level of 0.05 and delta of 0.05 and allowing for 20% drop-out across the trial, the sample size was calculated to be 18 participants, which allows for a complete cross-over randomization. We will employ some strategies suggested in the study of Little et al. (2012) for limiting data missing during conducting the trial [61].

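### Gait speed is the sole primary outcome but is measured on even and uneven surfaces, and the plan does not say which surface, or which pooled test, decides the primary result

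*Protocol article*

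**What the plan says.** The Primary and secondary outcomes section states: "The primary outcome will be gait speed, and secondary outcomes include other gait kinematics, muscle activation and functional mobility". The Statistical analysis section repeats it: "Gait speed will be the primary outcome in this study". Neither sentence mentions a surface, and Table 1 lists gait speed once, with no split.

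The Three-dimensional gait assessment section says that gait speed comes from the Vicon recording. In that recording "the participant will be asked to walk six times in a straight line, over even and uneven surfaces on the walkway".

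The Statistical analysis section sets out three analyses of the stimulation effect: paired t tests of pre against post within each visit, a linear mixed model for the main effect of the three stimulation conditions, and a mixed model for the interaction of time and stimulation "in the two conditions of even and uneven surfaces". One threshold covers them all: "values less than 0.05 will be considered significant". A Tukey correction is mentioned for post hoc comparisons where appropriate, without defining the family it covers.

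The Sample size section rests on a single gait-velocity measure from an earlier study, "measured by a 10-m timed walk", at a 5% significance level and 80% power. It does not give the surface of that walk.

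**The concern.** The interaction of time and stimulation is the term that asks whether the pre-to-post change differs between active and sham stimulation, so it bears most directly on the trial's question. It is to be examined under two surface conditions, and nothing says which of them carries the primary conclusion or that they are to be combined.

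Two things follow. If a result on either surface may be reported as a primary finding, the trial has more than one route to a positive primary result. And if one surface gives a P value below 0.05 and the other does not, the plan does not say what the trial has concluded, so the choice of surface could be made after the data are seen.

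**Working it through.** **The plan's own figure.** The stated sample size is 18, from delta 0.05, power 80%, significance level 0.05 and 20% drop-out. No standard deviation is given, so 18 cannot be reproduced, only back-solved. A paired t calculation with an SD of the difference of 0.06 gives 14 completers, and 14/0.8 = 17.5, rounded up to 18. That SD is an assumption. The calculation contains one gait-velocity measure and no division of the 5%.

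**Inputs for the error rate.** Two surfaces (Three-dimensional gait assessment; Statistical analysis) and a threshold of 0.05 (Statistical analysis), taken as two-sided because the plan does not state sidedness. The correlation between surfaces is not given, so a range is shown.

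**Reading 1: one interaction test per surface, each at 0.05.**

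- Upper bound: 0.05 + 0.05 = 0.10.
- Independent tests: 1 − 0.95² = 0.0975.
- Positively correlated tests, bivariate normal: 1 − P(|Z1| < 1.96, |Z2| < 1.96).

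| Assumed correlation | Chance of at least one false positive |
|---|---|
| 0.5 | 9.07% |
| 0.7 | 8.35% |
| 0.8 | 7.81% |
| 0.9 | 7.04% |
| 0.99 | 5.66% |

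The interaction has three stimulation conditions, so the actual test has 2 numerator degrees of freedom. A simulation of two correlated repeated-measures F tests (20,000 runs per setting) checks the approximation:

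| Assumed correlation | 18 participants | 15 participants |
|---|---|---|
| 0.5 | 8.8% | 9.5% |
| 0.8 | 8.2% | 8.1% |
| 0.9 | 7.4% | 7.4% |

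The two methods agree closely.

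**Reading 2: one model with surface as a factor and one interaction test averaged over surfaces.** There is one test at 0.05, so the error rate is 5% and surface adds nothing.

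**Between the readings.** A single model does not by itself settle the matter. It can yield the pooled interaction, the three-way term with surface, and an interaction within each surface. Unless one of these is named, a surface-specific result can still be put forward as primary.

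**Cost of keeping both surfaces as primary.** Splitting the level to 0.025 each multiplies the required number by ((2.241 + 0.842)/(1.960 + 0.842))² = 1.21. With the back-solved SD of 0.06, completers rise from 14 to 17 and recruits from 18 to 22 (17/0.8 = 21.25, rounded up). With 14 or 15 completers instead, a test that had 80% power at 0.05 has about 69% at 0.025.

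**The case against.** The strongest reply is that the plan never prescribes two tests. It speaks of the mixed model in the singular, and the sentence fits one model with surface as a factor as well as it fits two separate fits. The interaction is introduced as a further, potential effect and that sentence does not name gait speed, whereas the main-effect sentence does and mentions no surface. Model structure is also a matter that an article may leave to the full analysis plan. Both aims are labelled exploratory, and confidence intervals are promised.

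Much of this stands, and it limits what can be said. A reader might infer any of the following, and the document supports none of them:

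- **That testing each surface at 0.05 is an explicit rule.** It is the plain reading of one general threshold applied in two conditions, but it is not written as a rule.
- **That the paired t tests are run separately by surface.** The text does not say so.
- **That Tukey is stated to cover only the stimulation conditions.** The family is not defined, and the sentence comes directly after the carry-over analysis.
- **That the sample size already fixes the even surface.** The surface of the earlier study's walk is not given.

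What the reply does not remove is the gap itself. Which measurement is primary is for the protocol to settle. The exploratory label does not choose a surface, and the same part of the Background calls gait speed the main outcome measure.

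**Conclusion.** The point holds as a failure to fix the primary variable. Gait speed is measured on two surfaces, the key interaction is examined in both, and no surface or pooled test is named as the one that decides.

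The size depends on the reading. With one test per surface at 0.05, the false-positive chance for the primary outcome is above 5% and at most 10%, and about 7.0% to 9.1% for assumed correlations of 0.9 to 0.5. Having two surfaces should not be read as doubling the error rate: the same people walk both, so positive correlation is likely. With one pooled interaction test there is no inflation from surface. The lack of a rule for discordant surfaces does not rest on any of these assumptions. This is a moderate defect that should be corrected, and it does not by itself call for a larger trial.

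**What to change.** Before unblinding, name one primary test in the outcome and analysis sections. Either of these would do:

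1. **One surface.** State that gait speed on a named surface is primary and on the other surface secondary. The even surface is a reasonable choice, since the Study design section describes the target as natural walking over ground. The 10-m walk behind the sample size cannot be cited in support, because its surface is not given.
2. **One pooled test.** Fit a single mixed model with surface as a fixed factor, take the time-by-stimulation interaction averaged over surfaces as the only primary test at 0.05, and report the surface-by-time-by-stimulation term as secondary.

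Either option holds the surface-related error rate at 5%, leaves 18 participants unchanged and needs about a sentence. The price of the first is that an effect confined to the other surface becomes a secondary finding. The price of the second is that an effect on one surface only is diluted in the average and appears in a secondary term.

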#### Blinding and randomization

Blinding of the principal researcher will be achieved by using the “study mode” of the DC stimulator. The study mode activates active and sham stimulation with digital codes. To minimize biasing the outcomes, an independent researcher creates a list of participants using block randomization. A randomization sequence is produced through random permutations generated by a stochastic process program in R software version 3.3.4. The size of the blocks will be set to 3 with a ratio of 1:1 so that we need six blocks of the collection (1. ABC, 2. BAC, 3. BCA, 4. CBA, 5. CAB, 6. ACB). We will draw six numbers randomly and sequentially from this collection.

In the randomization list the preprogrammed digital codes of tDCS and the size of the cathode electrode will be assigned to each participant for each session and submitted to the principal researcher via a sealed envelope. The independent researcher provides the digital code and cathode electrode size for the principal researcher prior to each tDCS session. The DC stimulator display continues to indicate the impedance and the time in the same fashion for both active and sham tDCS. The principal investigator will be blinded to the participant and experimental condition during the processing and analysing of the gait data. However, in the case of an adverse event, where it is necessary for the principal researcher to know which stimulation the participant is receiving, the principal researcher will be unblinded. Data from the identifiers will be removed and replaced by codes. However, the data will be re-identifiable by using the code or linking the participant’s details to their allocation and to their different datasets. Reliability of blinding will also be assessed after each tDCS session by asking participants about the type of stimulation they believed they had received [58]. The principal investigator will also guess and record which stimulation type the participant had received.

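### An unnamed simple imputation is planned although the mixed model can use incomplete sessions; depending on the variant, it inflates type I error or biases the effect towards zero

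*Protocol article*

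**What the plan says.** The Statistical analysis section of the protocol article closes with one general rule: "Missing data will be handled using a simple imputation method [58". It does not name the variant, list the variables covered, or say how the rule relates to each analysis.

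The analyses that precede it are:
- The comparison of the three stimulation conditions, which "will be examined through a linear mixed model (LMM) with random intercepts". On the random part the text adds: "The LMM model will contain participants nested in sequence as a random effect".
- The within-visit comparison, made "using a paired *t* test to compare pre- and post-tDSC measures".
- A one-way ANOVA of the three pre-stimulation measures, and a Pearson correlation of baseline gait speed with physical activity.

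The Sample size section reaches 18 participants "allowing for 20% drop-out across the trial", so some missing data are foreseen.

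The cited reference does not settle the method from the text alone. The same number supports the adverse-effects scale in the intervention section and, under Blinding and randomization, the check made by "asking participants about the type of stimulation they believed they had received [58".

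**The concern.** The natural reading of a simple imputation is one filled-in value per gap, and the rule is not restricted to any analysis, so it reaches the mixed model for gait speed, the primary outcome. That model does not need it. Fitted by likelihood, it takes whatever sessions a participant has, and it is valid if missingness depends only on observed data. A filled value brings no new information but is counted as if it had been measured.

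Two kinds of damage can follow. If the filled values follow the fitted condition effects, residual variation looks too small and p values are too low. If they ignore the condition the participant would have received, they dilute the difference between conditions. The second matters here as much as the first, because the protocol intends to read effect size from the confidence interval.

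**Working it through.** **Inputs from the protocol.** There are 18 participants, three sessions each (54 visits), six sequences, a 5% level, a delta of 0.05 and a 20% drop-out allowance. The protocol gives no standard deviation, no unit for delta and no sidedness. I assume two-sided tests.

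**1. The planned sample size.** The stated basis is "considering a significance level of 5%, statistical power at 80%, significance level of 0.05 and delta of 0.05". Without a standard deviation, 18 cannot be verified. It is consistent with 14 completers: 14 / (1 - 0.20) = 17.5, rounded up to 18. With a paired t test, 14 completers and 80% power require a standardised difference of 0.81. If delta is a raw difference, the standard deviation of differences is then 0.05 / 0.81 = about 0.062. With 0.05, 0.08 or 0.10 instead, the total would be 13, 29 or 43.

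**2. How much is lost.** 20% of 18 is 3.6, so take 4 participants.
- Two leave after visit 1 and two after visit 2: 2×2 + 2×1 = 6 visits, 6/54 = 11%.
- All four leave after visit 1: 4×2 = 8 visits, 8/54 = 15%.

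**3. The mechanism in the simplest case.** Take one within-person difference, observed in 14 of 18 and mean-filled in 4. The sum of squares does not change, but the divisors do:

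reported SE / valid SE = sqrt[(13×14) / (17×18)] = sqrt(182/306) = 0.771.

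The test rejects when |t| on 13 degrees of freedom exceeds 2.110 × 0.771 = 1.627, which has probability of about 0.13. This shows the mechanism only; it is not the planned model.

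**4. The three-session design.** I simulated 18 participants over six sequences, with one gait-speed value per session, no period effect, missing completely at random, intraclass correlation 0.5, 0.8 or 0.9, and 2,500 runs per setting. The within-participant tests used equal the random-intercept model's tests when data are complete. The drop-out patterns are those of step 2.

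| Handling | Type I error of condition test | Model SE / empirical SE |
|---|---|---|
| Available data, no imputation | 0.044-0.057 (all settings, including step 6) | 0.98-1.03 |
| Condition mean | 0.071-0.115 | 0.85-0.91 |
| Regression on participant and condition | 0.118-0.165 | 0.77-0.83 |
| Last value carried forward | 0.043-0.054 | 0.985-1.03 |
| Participant mean | 0.043-0.054 | 0.985-1.03 |
| Grand mean | 0.039-0.049 | 0.985-1.03 |

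A check with an actual REML mixed model (250 runs, Monte Carlo error about 0.015) gave pairwise type I errors of 0.056 for available data, 0.100 for condition mean, 0.128 for regression and 0.064 for last value carried forward.

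**5. A true difference of 0.05** (intraclass correlation 0.8, standard deviation of differences 0.062, same patterns).
- Available data: estimate 0.050, reported SE 0.016.
- Last value carried forward and participant mean: 0.039-0.042, a loss of 16-22% (1 - 0.042/0.05 = 0.16; 1 - 0.039/0.05 = 0.22), with reported SE 0.013-0.014.
- Grand mean: 0.042-0.045.
- Condition mean and regression: unbiased (0.050), but with the SE problem of step 4.

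Carrying the last value forward costs little power (0.819-0.839 against 0.826-0.858 for available data). The damage is to the estimate and its interval.

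**6. A harsher case.** If 11 of 54 visits (20%) were missing, type I error would be 0.128-0.156 for condition mean and 0.234-0.243 for regression. The variants that ignore condition would shrink 0.05 to 0.035-0.040.

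**The case against.** The strongest reply is that the article fixes very little. It names no variant, no scope and no order relative to the model. It announces that the analysis plan will be provided before the database is opened, and variant and scope are details that an article may leave there. The rule might be meant for questionnaires or for the physical activity measure. The 20% is a recruitment allowance, not a forecast, and the protocol also plans attendance reminders and published strategies for limiting missing data.

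Much of this stands. It means the direction of the error cannot be read from the document. It does not remove the point: the article commits to simple imputation without restriction, and every variant tested did worse than no imputation on either error control or the estimate.

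A reader might infer more than the text supports:
- **That false positives will be inflated in general.** Only condition-mean and regression filling did this; the other three variants held about 5%.
- **That the type I error will be 13%.** That is the single mean-filled difference of step 3, not the planned three-condition model.
- **That a fifth of the data would be imputed.** Four participants leaving after visit 1 or 2 lose 11-15% of visits.
- **That a pre-stimulation value would be carried forward for a missed session.** A missed session has no pre-stimulation value of its own to carry.
- **That the rule should simply be struck out.** It is the only missing-data rule stated for the paired t tests, the ANOVA and the correlation, which are not likelihood-based.

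**Conclusion.** The point holds in a variant-dependent form. The plan applies an unnamed simple imputation where the mixed model can already use incomplete participants. With 4 of 18 dropping out, the cost is either a type I error of about 0.07-0.12 (condition mean) or 0.12-0.17 (regression), or shrinkage of a true 0.05 difference to about 0.039-0.045 (last value carried forward, participant mean, grand mean). Analysing the available data avoids both.

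These sizes rest on assumed intraclass correlations, an assumed standard deviation, missingness completely at random and no period effect. Informative drop-out or a trend across sessions would change them, particularly for carrying values forward. If few sessions are missed, the effect will be small. The documents do not support a claim that the planned p values will be too low; they support only that the rule, as written, permits that or a diluted effect, with no gain in return.

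**What to change.** Replace the imputation sentence with a scoped rule:
- **Mixed-model analyses of gait speed and the other outcomes:** no simple imputation. Fit by REML to all observed sessions, including participants with one or two, using small-sample degrees of freedom such as Satterthwaite.
- **Paired t tests, ANOVA and correlation:** use observed pairs or values.
- **Sensitivity analysis:** repeat the main comparison in participants who completed all three sessions.
- **Citation:** if imputation is kept for any other variable, name the variant and the variable, and state what the cited reference supports.

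The cost is a few lines of text before the database is opened, with no new data and less work than imputing. Confidence intervals may be slightly wider; in the simulation the SE was 0.016, against the 0.013-0.014 reported after carrying values forward or participant-mean filling.
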